**1.1.3.3 Phase III study of apatinib for the treatment of advanced gastric cancer**

Based on the results of the above phase I and II clinical studies, [name] and [name] conducted a multicenter, randomized, double-blind, parallel-controlled, superiority phase III clinical study in China (ClinicalTrials.gov registration number: NCT01512745) to further evaluate and validate the efficacy and safety of apatinib mesylate tablets versus placebo in patients with AGC. The primary endpoint was OS; the secondary endpoints were PFS, ORR, DCR, quality of life (QoL), and safety.

The phase III study enrolled a total of 273 AGC patients who did not respond to second-line systemic chemotherapy. The patients were centrally randomized at 2:1 into an experimental group (n = 181; apatinib) or placebo control group (n = 92; a placebo, namely, an apatinib simulation agent). The dose was 850 mg po, qd; each cycle was 28 days. Objective response was evaluated in accordance with RECIST 1.1, and AEs were closely monitored and evaluated in accordance with the National Cancer Institute (NCI) Common Terminology Criteria for Adverse Events, version 3.0 (CTCAE 3.0). The primary endpoint was OS; the secondary endpoints were PFS, DCR, ORR, QoL, and safety.

**Results:** After randomization, six untreated patients were excluded from analyses. A total of 267 randomized patients received at least one dose, including 176 patients in the experimental group and 91 patients in the placebo control group. Baseline data were comparable between the two groups. As of May 23, 2013, full analysis set (FAS) analysis, without considering crossover, showed that the mOS was 6.5 months in the experimental group and 4.7 months in the control groups, indicating that apatinib significantly extended survival by 1.8 months (*P* = 0.0149). Per-protocol set analysis indicated that the mOS was 7.6 for the experimental group and 5.0 months for the placebo control group, indicating that apatinib significantly extended survival by 2.6 months (*P* = 0.0027). When considering crossover, the mOS was 4.5 months in the control group after the data were adjusted for subjects who crossed over to the experimental group and was 2.0 months longer in the experimental group (HR = 0.646, *P* = 0.006), indicating that apatinib extended the mOS in the experimental group. The mPFS was 2.6 months in the experimental group and 1.8 months in the control group (*P* < 0.0001); the ORR was 2.84% in the experimental group and 0.00% in the control group (*P* = 0.1695); and the DCR was 42.05% in the experimental group and 8.79% in the control group (*P* < 0.0001). No significant between-group difference was observed in the change in QoL score (*P* > 0.05). For safety, apatinib was well tolerated in the experimental group, and the type and incidence of AEs were consistent with the findings in the apatinib phase II clinical study and with those for similar drugs on the market. Common AEs were leukopenia, neutropenia, thrombocytopenia, proteinuria, hypertension, HFS, fatigue, loss of appetite, diarrhea, and hoarseness; no unexpected AEs were observed. The incidence rate of AEs was 98.30% in the experimental group and 90.11% in the control group (*P* = 0.0038); the incidence of grade 3/4 AEs was 60.23% in the experimental group and 41.76% in the control group (*P* = 0.0000); the incidence of serious adverse events (SAEs) was 15.34% in the experimental group and 16.48% in the control group (*P* = 0.8598); and the incidence of drug-related SAEs was 6.25% in the experimental group and 6.59% in the control group (*P* = 1.0000). Most AEs were expected, tolerable, reversible, and controllable.

**Conclusion:** Apatinib exhibited a certain objective response and significant survival benefits in patients with AGC. Both primary and secondary efficacy measures, including OS, PFS, ORR, and DCR, were superior in the apatinib treatment group, indicating definitive survival benefits of apatinib. Moreover, apatinib was safe and well tolerated. The type and incidence of apatinib-related AEs were consistent with the adverse reactions of similar small-molecule VEGFR inhibitors on the market and the results of the apatinib phase II clinical study. No unexpected specific AEs were observed, and most AEs were reversed or controlled after drug discontinuation, dose reduction, or symptomatic care. Apatinib had no adverse effect on QoL. Therefore, apatinib can be used in clinical practice at the recommended dose of 850 mg qd ^[16.17]^. At the American Society of Clinical Oncology (ASCO) annual conference (June 2014), Prof, [name] of Fudan University Shanghai Cancer Center, on behalf of the study team, presented the results of the phase III clinical study of apatinib for the treatment of AGC, which attracted a great deal of attention ^[16]^.

Based on the above studies, the National Medical Products Administration (NMPA) approved apatinib tablets on October 17, 2014, as a category 1.1 new drug for the treatment of AGC that progresses after second-line chemotherapy failure.

**1.2 Rationale**

GC is a common malignancy worldwide. In China, its prevalence is especially high, and it is difficult to treat. Before apatinib was approved, no effective third-line treatment was available for AGC following second-line chemotherapy failure. During the same period of the clinical study of apatinib for the treatment of AGC, in 2014, a clinical study of ramucirumab (as monotherapy), a VEGFR-2 monoclonal antibody developed by Eli Lilly and Company (USA), was successful in patients with AGC or gastroesophageal junction cancer who did not respond to previous fluorouracil- or platinum-based chemotherapy (REGARD) ^[18]^, paving the way for ramucirumab to become the second (after trastuzumab) US FDA-approved targeted drug for GC and highlighting the importance of antitumor angiogenesis drugs for AGC, especially the feasibility of VEGFR-2 as a treatment target. However, ramucirumab is ineffective in Asian patients and is not yet available in China. Apatinib has been successful developed and has been approved by the NMPA; however, premarketing clinical studies were efficacy studies in certain patient populations with many exclusion criteria and may not reflect real-world data. Therefore, it is important to conduct prospective postmarketing studies to fill the gap between clinical practice and premarketing clinical studies to ensure rational drug use, safety, and effectiveness. During apatinib market authorization, the NMPA required Hengrui Pharmaceuticals Co., Ltd. To develop a rigorous risk management plan, conduct a phase IV clinical study to further observe and evaluate the large-scale postmarketing application of apatinib, collect detailed safety and efficacy data, and submit reports to the NMPA in a timely manner (see Annex).

**1.3 Disease population**

Patients with AGC or gastroesophageal junction adenocarcinoma following second-line chemotherapy failure

**2. Study Purpose**

**2.1 Primary purpose**

To evaluate the safety of apatinib mesylate tablets for the treatment of AGC or gastroesophageal junction adenocarcinoma following second-line chemotherapy failure.

**2.2 Secondary purpose**

To evaluate the effectiveness (OS, PFS, ORR, DCR, and QoL) of apatinib mesylate tablets for the treatment of AGC or gastroesophageal junction adenocarcinoma following second-line chemotherapy failure

**3. Study Design and Protocol**

**3.1 Description of study design**

This is a multicenter, prospective, open-label, single-arm, phase Ⅳ clinical study in China that is designed to evaluate the safety and effectiveness of apatinib mesylate tablets for the treatment of AGC or gastroesophageal junction adenocarcinoma following second-line chemotherapy failure. Therefore, the data collected and reported will comprehensively reflect the real-world data of apatinib mesylate tablets for the treatment of AGC or gastroesophageal junction adenocarcinoma following second-line chemotherapy failure.

**3.2 Dosing and drug management**

**3.2.1 Dosing schedule**

Apatinib mesylate tablets, 850 mg po qd, should be taken with warm boiled water 30 minutes after eating. The drug should be taken at the same time on each day whenever possible.

Note: To ensure patient safety and improve compliance, for female patients at an advanced age, with a poor condition or a small stature (≤ 50 kg) and who have unresected primary GC after four lines of chemotherapy, the initial dose may be reduced to 500 mg po qd, which can be increased as appropriate after 1-2 weeks or remain unchanged. The actual dose should be recorded.

**3.2.2 Dosing cycle**

Each dosing and observation cycle is 28 days. Responders (CR, PR, and SD) continue to take the drug until PD or death; the drug will be discontinued in the case of intolerable toxicity, patient withdrawal, or PD.

For patients with radiographically confirmed PD, the PI in the institution will promptly review the images and patient condition. Patients can continue treatment under close monitoring and follow-up, if they do not have intolerable reactions, their symptoms or QoL improved, the treating physician (investigator) believes that continuing to receive treatment increase survival benefits, and both the patient and PI agree to continue the treatment.

**3.2.3 Dose adjustment and drug discontinuation**

Refer to the NMPA-approved apatinib mesylate tablets package insert (see Annex).

**3.2.4 Drug management**

Apatinib mesylate tablets should be stored at room temperature (25°C or below), away from light in a sealed container. The shelf life is 2 years (tentative).

**3.3 Study duration**

The study is expected to last 5 years, including a 36-month enrollment period. After the end of treatment, each patient will be followed up until death or study withdrawal or 6 months after the last eligible patient is enrolled.

⚫ Planned first-patient-in/start date: April 1, 2015

⚫ Planned last-patient-in date: April 1, 2018

⚫ Planned last-patient-out/end date: October 1, 2018 (6 months after the last eligible patient is enrolled)

⚫ Planned database lock: December 31, 2018

⚫ Planned reporting date: April 1, 2019

**3.4 Study endpoints**

**Primary endpoint:**

⚫ **Safety:**

The incidence, severity, correlation, risk factors, measures taken, and outcomes of all AEs will be closely monitored and recorded in accordance with NCI CTCAE 4.0. Special attention will be paid to specific AEs, such as hypertension, bleeding, proteinuria, and HFS.

**Secondary endpoints:**

⚫ **Effectiveness:**

OS and PFS; ORR and DCR in accordance with RECIST 1.1; and QoL score

**4. Study Population and Patient Selection**

**4.1 Sample size**

The study will be conducted with 2000 patients at 100 sites across China.

**4.2 Inclusion and exclusion criteria**

**4.2.1 Inclusion criteria**

1. Age: 18 to 75 years old, men or women;

2. Pathologically and/or cytologically confirmed advanced gastric or gastroesophageal junction adenocarcinoma, with an extragastric measurable lesion (spiral computed tomography (CT) ≥ 10 mm, conforming to RECIST 1.1);

Note: Patients without any gastric or extragastric measurable lesion but with an observable lesion can be enrolled after a comprehensive evaluation by investigators from each institution to observe QoL and survival. These patients will be excluded from the evaluation of objective response.

3. Patients with AGC or gastroesophageal junction adenocarcinoma following ≥ second-line chemotherapy failure;

Note: (1) Definition of treatment failure: disease progression during treatment or tumor relapse and metastasis after treatment or intolerable toxicity; (2) for PD, each line of treatment is ≥ 1 cycle or longer with one or more chemotherapy drugs; pilot adjuvant/neoadjuvant therapy is allowed and will be considered first-line systemic chemotherapy for PD in the case of tumor relapse and metastasis during treatment or within 24 weeks after treatment; and (3) upfront therapy can be chemotherapy combined with molecular targeted drugs.

4. Eastern Cooperative Oncology Group (ECOG) performance status (PS) score: 0-2;

5. Normal vital organ functions based on the following standards:

(1) Complete blood count (CBC) (no blood transfusion within 14 days):

a. Hemoglobin (Hb) ≥ 90g/L;

b. Absolute neutrophil count (ANC) ≥ 1.5 × 10^9^/L; and

c. Platelet (PLT) count ≥ 80 × 10^9^/L.

(2) Serum biochemistry:

a. Bilirubin (BIL) < 1.5× upper limit of normal (ULN);

b. Alanine aminotransferase (ALT) and aspartate aminotransferase (AST) < 2.5× ULN; or < 5× ULN in the case of liver metastasis;

c. Serum creatinine (Cr) ≤ 1× ULN, endogenous creatinine clearance ≥ 50 ml/min (Cockcroft-Gault formula);

6. Expected survival ≥ 3 months;

7. The treating physician planned to use apatinib mesylate tablets for treatment;

8. Voluntary participation, with a signed informed consent form (ICF); and

9. Women with childbearing potential must have a negative pregnancy test (serum or urine) within 7 days of enrollment and be willing to use appropriate birth control throughout the observation period and for 8 weeks after the last dose of apatinib mesylate tablets. Men must be surgically sterile or agree to use appropriate birth control throughout the observation period and for 8 weeks after the last dose of apatinib mesylate tablets.

**4.2.2 Exclusion criteria**

1. Uncontrolled hypertension despite treatment with antihypertensive drugs (systolic blood pressure > 140 mmHg/diastolic blood pressure > 90 mmHg), grade ≥ Ⅱ coronary heart disease, arrhythmia (including corrected QT (QTc) prolongation > 450 ms in men or > 470 ms in women), or cardiac insufficiency;

2. Presence of several factors that may affect the absorption of oral drugs (such as swallow difficulty, nausea and vomiting, chronic diarrhea, and intestinal obstruction);

3. Important: patients at risk of gastrointestinal bleeding may not participate, including those with (1) active digestive ulcers, with fecal occult blood (++); (2) a history of melena and hematemesis within 3 months; and (3) fecal occult blood (+) and an unresected primary gastric tumor, if endoscopy indicates ulcerative GC with the possibility of lesion bleeding in the opinion of the treating physician;

4. Coagulopathy (international normalized ratio (INR) > 1.5× ULN, activated partial thromboplastin time (APTT) > 1.5 × ULN), with tendency to bleed;

5. Symptomatic central nervous system metastasis;

6. Pregnant or nursing women; and

7. Any patient deemed unsuitable for this study, as deemed by the treating physician.

**4.2.3 Drop-out/exclusion criteria**

1. Failure to take the drug per protocol, resulting in exclusion from effectiveness and/or safety evaluations; and

2. Major protocol deviation: Use of chemotherapy drugs and/or herbal preparations indicated for GC while in the study.

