| Inclusion and Exclusion Criteria | | **Inclusion Criteria:**  1. Age: 18 to 75 years old, men and women;  2. Pathologically and/or cytologically confirmed advanced gastric cancer or gastroesophageal junction adenocarcinoma, with an extragastric measurable lesion (spiral computed tomography (CT) ≥ 10 mm, conforming to Response Evaluation Criteria in Solid Tumors version 1.1 (RECIST 1.1));  Note: Patients without any gastric or extragastric measurable lesion but with an observable lesion may be enrolled after a comprehensive evaluation by investigators from each institution to observe quality of life (QoL) and survival. These patients will be excluded from the objective response evaluation.  3. Patients with advanced gastric cancer or gastroesophageal junction adenocarcinoma following ≥ second-line chemotherapy failure;  Note: (1) Definition of treatment failure: disease progression during treatment or tumor relapse and metastasis after treatment, or intolerable toxicity; (2) for progressive disease, each line of treatment is ≥ 1 cycle or longer with one or more chemotherapy drugs; pilot adjuvant/neoadjuvant therapy is allowed and will be considered first-line systemic chemotherapy for progressive disease in the case of tumor relapse and metastasis during treatment or within 24 weeks after treatment; and (3) upfront therapy can be chemotherapy combined with molecular targeted drugs.  4. Eastern Cooperative Oncology Group (ECOG) performance status (PS) score: 0-2;  5. Normal vital organ functions based on the following standards:  (1) Complete blood count (no blood transfusion within 14 days):  a. Hemoglobin (HB) ≥ 90 g/L;  b. Absolute neutrophil count (ANC) ≥ 1.5 × 10^9^/L; and  c. Platelet (PLT) count ≥ 80 × 10^9^/L.  (2) Serum biochemistry:  a. Bilirubin (BIL) < 1.5x the upper limit of normal (ULN);  b. Alanine aminotransferase (ALT) and aspartate aminotransferase (AST) < 2.5 × ULN; or < 5 × ULN in the case of liver metastasis; and  c. Serum creatinine (Cr) ≤ 1 × ULN, endogenous creatinine clearance ≥ 50 ml/min (Cockcroft-Gault formula).  6. Expected survival ≥ 3 months;  7. The treating physician planned to use apatinib mesylate tablets for treatment;  8. Voluntary participation, with a signed informed consent form (ICF); and  9. Women with childbearing potential must have a negative pregnancy test (serum or urine) within 7 days of enrollment and be willing to use appropriate birth control throughout the observation period and for 8 weeks after the last dose of apatinib mesylate tablets. Men must be surgically sterile or agree to use appropriate birth control throughout the observation period and for 8 weeks after the last dose of apatinib mesylate tablets.  **Exclusion criteria:**  1. Uncontrolled hypertension despite treatment with antihypertensive drugs (systolic blood pressure > 140 mmHg/diastolic blood pressure > 90 mmHg), grade ≥ Ⅱ coronary heart disease, arrhythmia (including the corrected QT (QTc) prolongation > 450 ms in men or > 470 ms in women), or cardiac insufficiency;  2. Presence of several factors that may affect the absorption of oral drugs (such as swallow difficulty, nausea and vomiting, chronic diarrhea, and intestinal obstruction);  3. Important: patients at risk of gastrointestinal bleeding may not participate, including those with (1) active digestive ulcers, with fecal occult blood (++); (2) a history of melena and hematemesis within 3 months; (3) for patients with fecal occult blood (+) and an unresected primary gastric tumor, if endoscopy indicates ulcerative gastric cancer with the possibility of lesion bleeding in the opinion of the treating physician;  4. Coagulopathy (international normalized ratio (INR) > 1.5 × ULN, activated partial thromboplastin time (APTT) > 1.5 × ULN), with bleeding tendency;  5. Symptomatic central nervous system metastasis;  6. Pregnant or nursing women; and  7. Any patient deemed unsuitable for this study by the treating physician.  **Drop-out/exclusion criteria:**  1. Failure to take the drug per protocol, resulting in exclusion from effectiveness and/or safety evaluation;  2. Major protocol deviation: use of chemotherapy drugs and/or herbal preparations indicated for gastric cancer while in the study.    **Termination criteria:**  1. Subject withdraws informed consent and requests an early exit;  2. Medical imaging indicates disease progression;  3. Becoming pregnant during the study;  4. Intolerable toxicity after two dose adjustments; and  5. In the opinion of the investigator, other circumstances that necessitate study exit. |

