**6.7 Procedures for patients who discontinue follow-up**

Patients may withdraw informed consent at any time and for any reason. Study withdrawal is considered only if the patient declines follow-ups to monitor his/her survival; otherwise, the patient is still considered in the study. The investigators will make every effort to contact the patients regularly to check their health status, at the very least survival.

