**8.4 Determining the relationship between adverse events and apatinib mesylate tablets**

The correlation between any AE and apatinib will be classified as “definitely”, “probably”, “possibly”, “unlikely”, and “unrelated” (see Table 1). The first three categories indicate that an AE is related to apatinib and will be included as the numerator when calculating the incidence of AE. All subjects will be included as the denominator for safety evaluations.

Table 1. Criteria for Determining the Relationship between Adverse Events and Apatinib Mesylate Tablets

| Criteria | Definitely | Probably | Possibly | Unlikely | Unrelated |
| --- | --- | --- | --- | --- | --- |
| Reasonable temporal relationship | Yes | Yes | Yes | Yes | No |
| Known drug reaction | Yes | Yes | Yes | No | No |
| Improvement after discontinuation | Yes | Yes | Yes or No | Yes or No | No |
| Recurrence after re-administration | Yes | ? | ? | ? | No |
| Additional possible explanations | No | No | No | Yes | Yes |

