**9. Statistical Processing**

**9.1 Analysis populations**

Safety set (SS): safety data set that will include all enrolled subjects who have received at least one dose of apatinib mesylate tablets and have at least one safety evaluation;

FAS: an intent-to-treat (ITT) data set that will include all randomized subjects who have received at least one dose of the apatinib mesylate tablets; subjects who did not receive any treatment after randomization and who do not meet inclusion criterion 2 will be excluded from FAS; and

Per-protocol set: a subset of FAS that will include all per-protocol, compliant subjects who did not receive any other GC treatment during the study and who have complete CFR data. Missing data will not be imputed.

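### The drop-out rule in 4.2.3 and the synopsis lets non-adherent, treated patients be left out of the safety evaluation, which contradicts the Safety Set in 9.1 and the denominator in 8.4

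*Protocol*

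**What the plan says.** Safety is the primary objective, and 9.2.1 makes AE incidence and severity the primary endpoints. The protocol says who counts in several places:

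- Section 4.2.3, item 1: "Failure to take the drug per protocol, resulting in exclusion from effectiveness and/or safety evaluations". The synopsis has the same rule: "Failure to take the drug per protocol, resulting in exclusion from effectiveness and/or safety evaluation".
- Section 4.2.3, item 2, calls the following a major deviation: "Use of chemotherapy drugs and/or herbal preparations indicated for GC while in the study". It states no consequence for any analysis.
- Section 9.1, Safety Set: "all enrolled subjects who have received at least one dose of apatinib mesylate tablets and have at least one safety evaluation".
- Section 8.4, on AE incidence: "All subjects will be included as the denominator for safety evaluations".
- Section 9.1, full analysis set (FAS): "all randomized subjects who have received at least one dose of the apatinib mesylate tablets", with a further exclusion tied to inclusion criterion 2.
- Section 9.1, per-protocol set: limited to "compliant subjects who did not receive any other GC treatment during the study", with complete data.
- Section 6.7: "Study withdrawal is considered only if the patient declines follow-ups to monitor his/her survival"; anyone else still counts as being in the study.

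**The concern.** The per-protocol set is the natural place for an adherence condition. Item 1 of 4.2.3 instead attaches it to the safety evaluation, which is the primary analysis. Adherence is observed after treatment starts and may itself result from toxicity, so selecting on it can remove the patients whose events the study is meant to count. The and/or in item 1 also leaves open which evaluation a given patient loses. In an open-label study that choice would be made with the patient's AEs already known.

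A second, smaller matter is the period covered by item 2 and by the per-protocol definition. Under 6.7 a patient in survival follow-up is still in the study. Read that way, chemotherapy given after progression and after the last apatinib dose would count as a deviation and remove the patient from the per-protocol set, although 6.5 expects such treatment and has it recorded.

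**Working it through.** **Step 1: one patient, each rule.** Take a patient who received at least one dose, had at least one safety evaluation, and then did not take the drug as required.

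| Place | In the safety evaluation? |
| --- | --- |
| 4.2.3 item 1 and synopsis | May be excluded |
| 9.1 Safety Set | In (no adherence condition) |
| 8.4 denominator | In (all subjects) |

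These cannot all be followed.

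**Step 2: does another section settle it?** Section 9.3.2 names the Safety Set for exposure and discontinuation, but its AE paragraph names no set. Section 4.2.4 lists termination criteria separately, so item 1 of 4.2.3 is not just a rule for stopping treatment. Section 9.3.1 has the SAP developed from the protocol, so the SAP would inherit both instructions. The conflict stands.

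**Step 3: possible size (illustration only).** The plan has no figure of its own to reproduce: 9.4 gives n = 2000 without a rate or precision target.

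Inputs:
- p = 0.6023, the grade 3/4 AE incidence on apatinib in phase III (1.1.3.3)
- n = 2000 (9.4)
- f, the share removed: assumed 10 to 20%
- r, the share of removed patients with a grade 3/4 event: assumed 80 to 90%

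Since p = f·r + (1 − f)·q, the rate in retained patients is q = (p − f·r)/(1 − f), and the bias is q − p = f(p − r)/(1 − f).

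| f | r | q | Bias (points) |
| --- | --- | --- | --- |
| 10% | 80% | (0.6023 − 0.08)/0.90 = 58.0% | −2.2 |
| 10% | 90% | (0.6023 − 0.09)/0.90 = 56.9% | −3.3 |
| 20% | 80% | (0.6023 − 0.16)/0.80 = 55.3% | −4.9 |
| 20% | 90% | (0.6023 − 0.18)/0.80 = 52.8% | −7.4 |

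The 95% half-width is 1.96·√(0.6023 × 0.3977/2000) = 2.1 points.

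The sign depends only on whether r is above or below p. In terms of a risk ratio R (removed versus retained patients), q = p/((1 − f) + f·R):

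- R = 1.25, f = 5%: 0.6023/1.0125 = 59.5%, bias −0.7 points
- R = 1.5, f = 20%: 0.6023/1.10 = 54.8%, bias −5.5 points
- R = 1: no bias
- R = 0.5, f = 5%: 0.6023/0.975 = 61.8%, bias +1.5 points
- R = 0.5, f = 20%: 0.6023/0.90 = 66.9%, bias +6.7 points

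**Step 4: other therapy and overall survival (OS).** Section 9.2.2 runs OS from consent to death from any cause and censors only at last follow-up. Neither that definition nor the FAS removes anyone for later treatment. Only the per-protocol set does, and it reaches treatment after apatinib only if its time phrase takes the meaning given in 6.7. A per-protocol OS estimate would then depend on later therapy, which a patient must live long enough to receive.

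**The case against.** The best defence is that 9.1 is the section that defines analysis populations, so a statistician would follow it and the looser wording in 4.2.3 would have no effect. Dose adjustment and discontinuation follow the package insert (3.2.3), and intolerable toxicity after two adjustments is a termination criterion (4.2.4). Toxicity-driven changes made under those rules are therefore not plainly failures of adherence. Poorly adherent patients may also have fewer events, because they were exposed to less drug.

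Most of this stands as a limit on what can be claimed: exclusion is permitted by one rule and not established as the one that will be used, and the direction of bias is open. It does not remove the contradiction. The protocol gives 9.1 no precedence, the exclusion is stated twice, and patients who skip or stop doses on their own account because of AEs are still exposed to it.

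The illustration has limits too. The documents give neither f nor r. The phase III rate was graded with CTCAE 3.0, whereas this study uses 4.0, and 8.4 counts only related events in the numerator.

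A reader might infer that any later gastric cancer therapy removes a patient from the OS analysis and biases it. The documents do not support that. Item 2 names only chemotherapy and herbal preparations indicated for gastric cancer and states no removal from OS, and the FAS is untouched. Section 9.3.3 names no set for OS, but that may properly be left to the SAP.

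**Conclusion.** The contradiction is established from the text: 4.2.3 and the synopsis permit an exclusion from the safety evaluation that 9.1 and 8.4 do not allow. It concerns the primary endpoint and should be reconciled.

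Bias is possible but not demonstrated. Under the assumptions above, the reported grade 3/4 rate would be 2.2 to 7.4 points too low, from about one to more than three times the half-width. These figures hold only if 4.2.3 is applied, 10 to 20% are removed, and 80 to 90% of those had an event. It would be wrong to conclude that the rule necessarily lowers AE rates.

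The time phrases on other therapy need clarifying as a secondary matter, with a possible effect on a per-protocol OS estimate only.

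**What to change.** - In 4.2.3 and the synopsis, delete the exclusion from effectiveness and safety evaluations. State that non-adherence, or use of chemotherapy or herbal preparations indicated for gastric cancer, is a protocol deviation that affects membership of the per-protocol set only.
- State that the Safety Set and FAS apply as defined in 9.1 regardless of adherence, and that follow-up for AEs and survival continues. Do not write that every dosed patient belongs to both sets: the Safety Set also needs one safety evaluation, and the FAS has its exclusion tied to inclusion criterion 2.
- In item 2 of 4.2.3 and in the per-protocol definition, tie the time phrases to the apatinib treatment period. Section 6.5 already uses the last dose as the start of posttreatment follow-up.

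The cost is amendment wording only. No dose, visit or sample size changes.
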